**2.2 Safe behaviors**	
a. Using child restraints for child when taking a car	
b. Requiring child to wear safety protective equipment when riding a bicycle or scooter	
c. Testing water temperature before bathing the child	
d. Pouring the water out of the bathtub immediately after using it	
e. Keeping hot substances and lighters out of child’s reach	
f. Keeping sharp objects out of child’s reach	
g. Keeping medicines, detergents, sanitizers, antiseptics, and pesticides out of child’s reach	
h. Keeping small objects out of child’s reach	
**3. Home environment safety** (with six response options: completely like this, mostly like this, partly like this, mostly unlike this, completely unlike this, and not applicable)	
**3.1 Risky home environment items**	
a. Tablecloths or cloth coverings on tables and cabinets can be pulled	
b. Power cords for electric appliances are not fixed	
c. There are tables, chairs stools, or cabinets beside balconies or windows	
d. There are water spills or oil stains on the floor	
e. There are toys or dolls in the child’s bed	
f. Kitchen supplies like pots, bowls, plates, and cups are placed in child’s reach	
g. Plastic bags or cling wraps are placed in child’s reach	
h. Large round foods like grapes or nuts are placed in child’s reach	
i. Chemicals are stored in non-original containers	
**3.2 Safe home environment items**	
a. There are protectors on sharp corners	
b. Switches of water dispensers and gas stoves are equipped with protective devices	
c. Balconies and windows are equipped with guard railings	
d. Child’s bed is equipped with guard railings	
e. There are soft protective materials on the floor beside the child’s bed	
f. Water storage supplies are lidded	
g. There are anti-skid devices in the washing and bathing places	

### Pilot testing

Prior to commencing the formal study, we will recruit 60 caregivers of preschoolers to participate in feasibility testing (30 from Yang County and 30 from Shicheng County). During a one-week pilot testing phase, participants will complete two online questionnaires. One will collect complete data listed in Table 1 as well as socio-demographic factors, and the other will assess the user’s experience concerning the contents, readability, functions, interface, operability, and usability of the app. The results of feasibility testing will be used to finalize the survey questionnaire and make final refinements to the app.

### Collection of formal data

Survey data will be collected at baseline and every 3 months during the entire 18-month follow-up period. All data will be collected online through the app and stored in a password-protected backend database. If caregivers fail to complete an app-based online survey, designated members of the coordinating group will remind or guide them. When needed, a phone-based survey interview will be employed.

Participant engagement data will be gathered and stored in the backend database automatically through embedded tracking of app usage. Data to be collected include: (1) the frequency of logins, (2) time span from login to logout each time, (3) frequency of reading instructional materials, (4) time spent on learning instructional materials, (5) number of reading or bookmarking knowledge disseminations, (6) number of posting comments on knowledge disseminations, (7) number of likes clicked on knowledge disseminations, (8) frequency of joining a discussion in the online forum, (9) number of bookmarked online forum themes, (10) number of comments posted in the online forum, and (11) number of likes clicked in the online forum.

### Data analysis plan

Primary data analysis will follow an intention-to-treat (ITT) approach. Descriptive statistics will be calculated for socio-demographic variables and primary and secondary outcomes, including mean (or median) and standard deviation (or range and interquartile range) for continuous variables, and frequency and proportion for categorical variables. For each time point, Chi-square and two-sample *t*-tests (or Wilcoxon rank sum test if data are skewed) will be used to examine the differences in outcome measures between intervention and control groups for categorical and continuous variables, respectively. Trend tests or analysis of variance (ANOVA) will used to detect within-group differences across the six follow-up visits.

Generalized Estimating Equation (GEE) will be used to assess the overall effectiveness of the app-based intervention, while adjusting for socio-demographic variables, engagement, and baseline injury events.

A Generalized Linear Mixed Model (GLMM) will be used to verify the GEE results. With GLMM, missing values can be imputed using the Expectation Maximization (EM) algorithm. A per-protocol (PP) sensitivity analysis will be conducted to validate ITT results. All statistical analyses will be performed using R version 4.0.4. All statistical tests will be two-sided at the significance level of 0.05.

Subgroup analyses will be conducted to assess the impact of socio-demographic factors on the intervention effect, including gender and age of children and their caregivers, type of children’s caregivers (e.g., parents, grandparents, or others), education level of caregivers, and household income per capita per month. Subgroup analyses will employ the same statistical methods used for the primary analyses.

This study will strictly adhere to the Consolidated Standards of Reporting Trials (CONSORT) 2010 statement [37] and the Standard Protocol Items: Recommendations for Interventional Trials (SPIRIT) 2013 statement [38] to analyze the data and report the results.

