### Sample size

Based on previous literature [29], we conservatively hypothesize that the unintentional injury incidence of rural preschoolers aged 3–6 years old in project sites is 30% in the past 18 months. On the basis of a previous report [30], we assume the effect size of the app intervention to be 0.80 (incidence rate ratio) compared to traditional unintentional injury prevention intervention. In addition, we assume an intra-class correlation (ICC) of 0.005 with a cluster size of 150 children per preschool [31], and an allocation ratio of 1:1 between intervention and control groups. Considering extensive strategies will be adopted to increase retention in the study, we assume an attrition rate of 15% for the 18-month follow-up. Given these assumptions, a minimum sample size of 3508 caregivers is needed for the study to achieve a statistical power of 80% at the 0.05 significance level. As many rural preschools have more than 150 children in the study sites we select, 24 preschools will be ample to recruit the needed sample size.

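### The between-arm tests planned at each visit ignore preschool clustering: at the protocol's own ICC, a nominal 5% test has a true error of about 12% to 14%

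*Protocol article*

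**What the plan says.** All references are to the Protocol article.

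- **Design.** Preschool recruitment makes the preschool the unit of randomisation, with 24 preschools, 12 per arm.
- **Sample size.** The calculation allows for clustering: "we assume an intra-class correlation (ICC) of 0.005 with a cluster size of 150 children per preschool". With 15% attrition it concludes that "a minimum sample size of 3508 caregivers is needed for the study to achieve a statistical power of 80% at the 0.05 significance level".
- **Data analysis plan, per-visit comparisons.** The plan reads "For each time point, Chi-square and two-sample" t-tests, with the rank test as the alternative: "or Wilcoxon rank sum test if data are skewed) will be used to examine the differences in outcome measures between intervention and control groups". No cluster adjustment is attached to any of these tests.
- **Data analysis plan, error level.** "All statistical tests will be two-sided at the significance level of 0.05".
- **Data analysis plan, change over time.** "Trend tests or analysis of variance (ANOVA) will used to detect within-group differences across the six follow-up visits".
- **Data analysis plan, main model.** "Generalized Estimating Equation (GEE) will be used to assess the overall effectiveness of the app-based intervention", with a GLMM to verify the result. The section names no clustering unit, type of standard error or reference distribution for the GEE, and no random effects for the GLMM.

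**The concern.** Children in one preschool share teachers, surroundings and the assigned version of the app, so their outcomes are correlated. The protocol accepts this when it sets the sample size, but the per-visit tests it names take no account of it. A chi-square, t or Wilcoxon test on individual children uses a variance that is too small by the design effect, so its p-values are too small whenever the ICC is positive.

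The tests are to be run at every time point, on primary and secondary outcomes, at 0.05. Readers would therefore see a series of p-values whose real error rate is more than twice the nominal one under the protocol's own assumption. Isolated significant visits could be read as evidence of an effect that the cluster-adjusted analysis does not support. This is a commitment written into the article, not a detail left open: an analysis plan that adjusted these tests would be changing what the article says.

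**Working it through.** **Inputs from the protocol.** Control incidence 30% over 18 months; ratio 0.80, hence 24% in the intervention arm; ICC 0.005; 150 children per preschool; attrition 15%; power 80%; two-sided 0.05; 24 preschools; N = 3508.

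**1. Does the stated sample size use the design effect?**
- Design effect: 1 + (150 − 1) × 0.005 = 1.745.
- Unpooled two-proportion formula: (1.960 + 0.842)² × (0.30 × 0.70 + 0.24 × 0.76) / 0.06² ≈ 855.5 per arm.
- Total: 2 × 855.5 × 1.745 / 0.85 ≈ 3513, or 3514 after rounding up per arm.
- The pooled-variance version gives 859 per arm and a total of 3528.
- Both lie within 0.6% of 3508. Without the design effect the total would be about 2 × 859 / 0.85 ≈ 2021. The stated figure therefore does include clustering.

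**2. True error of an unadjusted per-visit test.** If the true variance is the design effect (DE) times the assumed one, a two-sided test at 1.96 rejects a true null with probability 2 × [1 − Φ(1.96/√DE)].
- 150 per preschool: DE = 1.745; 1.96/√1.745 = 1.484; error = **13.8%**.
- After attrition: 3508 × 0.85 / 24 ≈ 124.2 per preschool; DE = 1 + 123.2 × 0.005 = 1.616; 1.96/√1.616 = 1.542; error = **12.3%**.
- Simulation as a check (40,000 null trials, 12 + 12 preschools of 124 children, risk 0.27, ICC 0.005): 12.4%.

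**3. Sensitivity to the ICC.** The protocol's 0.005 serves the 18-month injury calculation. Values for a single quarter, or for attitude, behaviour and home-safety scores, are not given, so the other rows are assumptions.

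| ICC | Error at 124 per preschool | Error at 150 per preschool |
|---|---|---|
| 0.001 (assumed) | 6.4% | 6.7% |
| 0.005 (protocol) | 12.3% | 13.8% |
| 0.01 (assumed) | 19.0% | 21.4% |
| 0.02 (assumed) | 29.2% | 32.6% |

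**4. The GEE, conditionally.** Suppose it were clustered on preschool with an uncorrected sandwich standard error and a normal reference. The article does not say this. Simulated error at ICC 0.005 is then about 7.4% with equal preschool sizes, 8.0% with an assumed coefficient of variation of size of 0.4, and up to about 9% with 0.6. With a simple small-sample correction and a t reference on 24 − 2 = 22 df, it is 5.1% for equal sizes and 5.6% for a coefficient of variation of 0.4.

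**5. The within-group ANOVA.** It was simulated as a one-way ANOVA treating all six reports per child as independent, with no true time effect. The rejection rate was 4.7%, 2.2%, 0.1% and 0.0% at within-child correlations of about 0, 0.2, 0.4 and 0.6. It exceeded 5% only when an assumed preschool-by-time variance was large enough: 10% with variance 0.005 and correlation 0.4, but 2.6% with variance 0.002 and the same correlation.

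**The case against.** The strongest reply is that these tests are supporting material. They stand beside the descriptive statistics, the primary outcome is cumulative over 18 months and not a per-visit contrast, and overall effectiveness is assigned to the GEE. That is correct, and it limits the weight of the point. It does not remove it, because the tests compare the randomised arms and are to be judged at 0.05.

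A second reply is that a single error figure is overprecise, since the protocol's ICC belongs to the 18-month injury outcome. That also stands, which is why a range is given. The direction does not change for any positive ICC.

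Two stronger readings are tempting, and the document supports neither.

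- **That the primary GEE is itself invalid.** A reader might infer this from the absence of any mention of preschool in the Data analysis plan. If the child were the clustering unit, preschool correlation would indeed be ignored; if an uncorrected sandwich error were used with 24 preschools, the error would be moderately inflated. But the article states neither, and a condensed article may leave these settings to the statistical analysis plan. The figures in step 4 describe a possible implementation, not the plan.
- **That the within-group ANOVA p-values are also too small.** Ignoring positive correlation within a child overstates the error variance of changes over time, and a constant preschool effect cancels. The p-values are then generally too large, unless preschool-by-time variation dominates. The text also does not exclude a repeated-measures ANOVA, and it does not present within-group change as a treatment effect.

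**Conclusion.** The point holds for the between-arm tests at each time point. By the protocol's own ICC and cluster size, a nominal 5% test has a true error of about 12.3% to 13.8%, and about 6% to 33% over assumed ICCs of 0.001 to 0.02. This rests on the tests being run in their standard, unadjusted form, which is how the article names them, and on equal preschool sizes; unequal sizes make it somewhat worse (13.3% in simulation at 124 per preschool with a coefficient of variation of 0.4).

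It should be fixed before analysis, but it does not by itself undermine the primary conclusion, which depends on the GEE. How the GEE handles preschool is a matter for confirmation.

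**What to change.** 1. **Per-visit comparisons (the correction).** Make the between-arm tables at each visit descriptive, without p-values. Alternatively, take the per-visit contrasts from a model that accounts for preschool clustering, for example arm-by-visit terms in the GEE or GLMM.
2. **GEE (conditional recommendation).** Confirm, or state, that it clusters on preschool with a small-sample-corrected standard error (Kauermann-Carroll or Mancl-DeRouen, for instance) and a t reference on about 22 df.
3. **Tests over the six visits.** If within-group tests are kept, use a repeated-measures model.

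The cost is analysis wording, standard R code and wider confidence intervals for the per-visit contrasts. If item 2 is not already intended, the t reference also shows a little less power than planned. With 3508 × 0.85 / 2 ≈ 1491 analysed per arm, 30% against 24% and a design effect of 1.745, the standard error of the difference is √(0.3924 × 1.745 / 1491) = 0.0214. The ratio 0.06/0.0214 is about 2.80, and power on 22 df is about 76%. With the post-attrition design effect of 1.616 it is about 79%.

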Successful delivery of mHealth interventions does require the recipients to have smartphones. According to *the 47th China Statistical Report on Internet Development* [15], the number of rural internet users has increased rapidly in China over the last decade, reaching 309 million by December 2020. Stated differently, internet penetration in rural areas of China has reached 55.9% and is anticipated to continue to grow rapidly [15]. This trend supports design and implementation of mHealth intervention programs for rural Chinese populations, including efforts to prevent child unintentional injury in rural areas of China.

Many mHealth interventions have been developed already for chronic disease management, maternal and infant health promotion, infectious disease prevention and control, and health services delivery [16–18], but our extensive literature searches find just 8 randomized controlled trials targeting child unintentional injury prevention via mHealth strategies [19–26]. This includes 4 trials in the United States, 1 in Australia, and 3 in China. All the eight programs were designed for urban children and implemented an intervention time interval of 8 months or less. Furthermore, seven trials used knowledge, attitudes, or behaviors as primary outcome measures to evaluate effectiveness rather than actual injury events. The only trial that examined actual changes in injury incidence rate used a 6-month intervention period and did not demonstrate the significant effectiveness [24]. User fatigue and resultant non-compliance to the intervention, plus substantial attrition from the study, were interpreted as reasons that the intervention was ineffective [27]. So far, the long-term effectiveness of mobile health technology in reducing actual child injury incidents has not been assessed in any published study.

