### Participant recruitment

Eligible participants meet the criteria: being the primary caregiver of a preschooler attending the included schools.

Potential participants will be excluded from this study if they meet any of the following criteria: (1) unwilling to participate in this study; (2) do not own a smartphone or cannot operate the app independently; (3) cannot read text messages; or (4) expect to move to another city with their children during the study time period. If an eligible caregiver care for more than one eligible preschooler, we will enroll only the youngest child.

In coordination with local cooperative partners (governmental departments and agencies), we will recruit class teachers and school staffs to help coordinate recruitment of study participants in each selected preschool. Those individuals will inform eligible caregivers about the study via multiple existing preschool-family communication channels, such as social media platforms (WeChat or QQ), school apps, printed briefing materials and oral notification. Caregivers who agree to participate will be provided an invitation letter that includes the benefits and responsibilities of participating in this study and instructions to download, install, sign up, log in and use the randomly-assigned app. Moreover, all caregivers who agree to participate will receive a short online guidance video that detailedly introduces basic information about the study and educates the participants on how to utilize the app.

When participants log into the app for the first time, they will be invited to complete and submit the informed consent documentation online. All consenting participants will then complete the baseline survey, which collects information about unintentional injuries the child experienced in the past 3 months as well as information on socio-demographic characteristics, caregiver’s attitudes, caregiver-reported behaviors surrounding child unintentional injury prevention, and caregiver-reported home environment safety based on the standardized safety checklist over the prior week.

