### Interventions

Both the intervention and control groups will receive routine school-based education from each included preschool plus the app-based education programs. Routine school-based education encompasses health education, including injury prevention, that is performed by preschool teachers. This education is typically based on the suggested course from the Ministry of Education of China and influenced somewhat by the teacher’s knowledge and preferences for teaching injury prevention to children.

The basic framework for child unintentional injury prevention in the app is based on previous theories and research [32]. It comprises four active modules: (1) content learning, including a series of instructional materials to impart basic and practical knowledge and skills; (2) social interaction, consisting of an online forum, online expert consultation opportunities, and locations for users to leave comments that facilitate communication among users and between users and experts; (3) survey and feedback, used for online survey data collection and user’s suggestions, and for experts to reply to user queries; and (4) a personalizing module, allowing users to customize the color scheme of their app and to display the user’s personal learning progress. The four active modules will be identical for both groups during the program and are detailed along with the app design and other functions in a previous publication [32].

The intervention will differ between the intervention and control groups based on the learning contents they receive. The control group will receive a parenting health education program covering topics like pediatric disease risks, childhood nutrition, early childhood development, and child health care. It will exclude any explicit information about unintentional child injury prevention. The intervention group will receive all contents the control group receives plus additional components focused on prevention of common child unintentional injuries in rural areas (e.g., road traffic injury, falls, drowning, suffocation, poisoning, burning, scalding, electric current burns, and other injuries caused by animate or inanimate mechanical forces).

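### The GEE for overall effectiveness adjusts for app engagement, which is recorded after randomisation, so its treatment coefficient need not be the total effect of assignment

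*Protocol article*

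**What the plan says.** The Data analysis plan opens with the principle: "Primary data analysis will follow an intention-to-treat (ITT) approach". It then names the main model: "Generalized Estimating Equation (GEE) will be used to assess the overall effectiveness of the app-based intervention". The covariates of that model are listed next: "while adjusting for socio-demographic variables, engagement, and baseline injury events". The Abstract gives the GEE the same role.

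Collection of formal data defines the covariate: "Participant engagement data will be gathered and stored in the backend database automatically through embedded tracking of app usage". Its eleven items cover logins, session length, reading and learning, bookmarks, comments, likes and forum activity. The baseline survey described under Participant recruitment contains no engagement measure, and none could exist, because caregivers who agree to take part are given "instructions to download, install, sign up, log in and use the randomly-assigned app".

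Under Interventions, the four app modules are the same in both arms but the learning content is not: "The intervention group will receive all contents the control group receives plus additional components focused on prevention of common child unintentional injuries".

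**The concern.** An intention-to-treat estimate of effectiveness answers one question: what happens to injury when preschools are assigned to the injury-prevention app rather than the control app. Randomisation protects that comparison as long as the model conditions only on variables fixed before allocation. Socio-demographic variables and baseline injury events qualify; engagement does not.

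Two things can go wrong if assignment alters the amount of app use. First, any benefit that arises because the intervention app is used more (or less) is adjusted away. Second, engagement probably also reflects caregiver traits that bear on injury and are not measured. Comparing arms at equal engagement then compares caregivers who differ in those traits, an imbalance that randomisation had excluded.

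The protocol itself treats engagement as relevant to effect. Of the earlier urban trial it says: "User fatigue and resultant non-compliance to the intervention, plus substantial attrition from the study, were interpreted as reasons that the intervention was ineffective". It also devotes a section to raising engagement. The trial's main claim, and the planned free distribution of the app, rest on this coefficient.

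**Working it through.** **1. The plan's own figure.** Inputs from Sample size: 30% against 0.80 × 30% = 24%, ICC 0.005, 150 children per preschool, 15% attrition, 80% power, alpha 0.05 (two-sided according to the Data analysis plan).

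- Design effect: 1 + (150 − 1) × 0.005 = 1.745.
- Per arm, unpooled variance: (1.96 + 0.842)² × (0.30 × 0.70 + 0.24 × 0.76) / 0.06² ≈ 855.5.
- Total: 2 × 855.5 × 1.745 / 0.85 ≈ 3,513 (3,527 with pooled variance). The stated 3,508 is reproduced.

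This calculation contains no covariate adjustment, so it does not depend on whether engagement is in the model.

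**2. Effect running through the amount of engagement (assumed shares).** If a share s of the log effect runs through engagement, the adjusted ratio is 0.80^(1 − s).

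- s = 25%: 0.80^0.75 = 0.846. s = 50%: 0.80^0.5 = 0.894.
- Analysed per arm: 3,508 × 0.85 / 2 ≈ 1,491; effective number 1,491 / 1.745 ≈ 854.
- Power = Φ(difference / SE − 1.96), with SE = √{[p1(1 − p1) + p2(1 − p2)] / 854}.

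| Ratio | p2 | Difference / SE | Power |
|---|---|---|---|
| 0.80 | 0.240 | 0.060 / 0.0214 = 2.80 | 80% |
| 0.846 | 0.254 | 0.0462 / 0.0216 = 2.14 | 57% |
| 0.894 | 0.268 | 0.0317 / 0.0218 = 1.45 | 31% |

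This puts the attenuated ratio into the plan's own test; any change in standard error from the extra covariate is ignored.

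**3. Path through an unmeasured caregiver trait (assumed inputs).** Let engagement, in SD units, be g × arm + 0.5 × trait + noise. Let the trait have log-OR b per SD on injury, and let the app have no effect. Within an arm, the expected trait at a given engagement is 0.5 × (engagement − g × arm). The arm coefficient after adjustment is therefore approximately −0.5 × g × b instead of 0.

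| g | b = +0.3 | b = −0.3 | b = −0.6 |
|---|---|---|---|
| 0 | 1.00 | 1.00 | 1.00 |
| 0.1 | 0.99 | 1.02 | 1.03 |
| 0.3 | 0.96 | 1.05 | 1.09 |
| 0.6 | 0.91 | 1.09 | 1.20 |

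Entries are exp(−0.5 × g × b). Simulated logistic regressions give slightly smaller extremes, roughly 0.92 to 1.18. The direction depends on the sign of b.

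**4. Both mechanisms together.** A Poisson simulation used 1,000,000 children, a true total ratio of 0.80, arm differences of 0.25 to 0.5 SD and a trait log rate ratio of −0.3. Without engagement in the model the ratio was 0.80 to 0.81. With engagement, and 25% to 50% of the log effect running through it, the ratio was 0.88 to 0.97. With no arm difference in engagement, both models returned 0.80. Clustering was left out because it does not move the point estimate.

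**The case against.** The strongest reply is that the arms may engage almost equally. The modules are identical, segments go out seven times a week in both groups, reward points are offered in both, and the protocol says delivery differs only in content. With equal engagement nothing shifts, and a difference of 0.1 SD moves a true null only to about 0.99 to 1.03. This stands as a limit on size. It does not make the covariate safe, because content differs by arm and equal engagement cannot be presumed before the data are seen.

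A reader might infer that, because reading injury content is how the app works, adjusting for engagement absorbs the whole effect. The documents do not support that. The logged measures are generic and exist in both arms, while control content has no explicit injury-prevention material. Much of the mechanism is therefore an arm-by-engagement interaction, which a main-effect covariate does not remove. When an effect running entirely through that interaction was simulated, the ratio was 0.80 with and without adjustment at equal engagement. With engagement 0.3 SD higher in the intervention arm it moved only from 0.75 to 0.77. Only the part that runs through a change in the amount of engagement is lost.

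It can also be said that intention-to-treat fixes who is analysed in which arm, and that nothing in the plan drops or reassigns anyone. That is correct. The objection concerns what the coefficient estimates, not the analysis population.

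Finally, the plan includes chi-square and t-tests at each time point without engagement. They mitigate only in part: they are not the overall effectiveness analysis and, as described, they take no account of clustering by preschool. The per-protocol analysis answers a different question.

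**Conclusion.** The covariate list is wrong as written. The model for overall effectiveness conditions on a variable that is post-randomisation by the protocol's own definition, under an intention-to-treat label, and no GEE without it is named. That much does not depend on any assumption.

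Whether the estimate would be biased, how much and in which direction are not settled by the documents. A reader might conclude that it is biased, or biased towards no effect; neither is supported. The lower bound is no shift, when engagement does not differ between arms. The range of roughly 0.92 to 1.18 under a true null, and the power of 57% or 31%, hold only under the assumed arm differences, trait associations and mediated shares, for which the protocol gives no figures. The range includes a falsely favourable result as well as a masked benefit.

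Nor does the text show that the GLMM carries the same fault: it gives no covariates for that model. But a model meant to verify the GEE would naturally share its covariates, and the subgroup analyses are to use the primary methods, so the problem may carry over.

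**What to change.** In the Data analysis plan, delete engagement from the covariates of the primary GEE and keep only the pre-randomisation variables already named: socio-demographic variables and baseline injury events. State that the GLMM used to verify the GEE has the same covariate set, and that the subgroup analyses follow it.

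Report engagement only in a separately labelled secondary analysis. If that includes a dose-response analysis within the intervention arm, state that the comparison is not randomised and is confounded by caregiver characteristics.

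The cost is one word in the covariate list and two or three added sentences. The sample size of 3,508 stays as it is, and the engagement data are still collected as planned.
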